**Ministry of Health (MoH) of the Transitional Islamic State of Afghanistan in Kabul**

**Background**

The intralesional and systemic treatment of active **anthroponotic cutaneous leishmaniasis** (ACL) with pentavalent antimonials (SbV), which are in use since 1929, are still the current main therapeutic strategy in Afghanistan. The intralesional approach is unsatisfactory because of pain and negative toxic effects on wound healing. In approximately 10 % of the cases both systemic as well as intralesional administrations require discontinuation because of allergy. Other serious side-effects are myalgia, pancreatitis, renal failure, peripheral neuropathy, hepato- and cardiotoxicity.

In contrast to the systemic and mucocutaneous forms of leishmaniasis, which are predominant on the Indian subcontinent and in South America respectively, ACL, the overwhelming form of *Leishmania* disease in Afghanistan, is a self-limiting parasitic infection. In patients in Afghanistan, 2 to 24 months after the transmission of *Leishmania (L.) tropica* by the sand fly (*Phlebotomus sergenti*) (incubation period), a shiny papule slowly growing to a nodule is formed, which ulcerates centrally, enlarges centrifugally and has the tendency to heal after one to two years without any treatment leading to a permanent immunity in ca. 90 % of the cases. In 10% of the cases relapses with scant parasites in the lesion, an increased delayed type hypersensitivity (DTH) reaction to parasite antigens and/or resistance to SBV treatment occur. *L. tropica* rarely spreads to the viscera.

However, terrible **hygienic conditions** in the extremely dry and dusty climate of Afghanistan constitute serious problems for any long-lasting wound in this country. Actually, Kabul is without any sewage system for its 3.5 million inhabitants. Here, chronic ulcers rapidly cover with thick crusts which are super-infected with fungi and bacteria and lead to a high incidence of chronic eczemas and to disfiguring scars that result in social exclusion of girls and women, if they are located in the face.

**Pharmaceutical sodium chlorite** entered the German Drug Codex in 1990 under DAC N-055, i.e. 7 years after a pharmaceutical sodium chlorite preparation had been approved for moist wound care management by the German Health Authorities, the former BGA in Berlin, under the trade name of OXOFERIN®. Originally, it was believed that technical grade sodium chlorite purchasable as a chemical compound bulk ware could do the “drug job” of OXOFERIN®. However, only recently it became clear that chlorite which had been produced from chlorine dioxide in a chlorate free manner by the addition of peroxide under alkaline conditions, lost its strikingly positive clinical effects on wound healing, which have been described in several publications for the registered finished chlorite solution OXOFERIN® , after it had been either concentrated by evaporation or purified through crystallisation. It is currently believed that alkaline chlorate-free chlorite production with chlorine dioxide as starting material leads to the formation of the salt of peroxychloric acid , which yields pure chlorite and oxygen when evaporated to dryness.

Thanks to financial support in Germany by Caritas International, Diakonie – Katastrophenhilfe, and BASF AG Ludwigshafen, the non-profit non-governmental organisation (NGO) “Waisenmedizin (WM e. V.)” in Freiburg, was able to produce pharmaceutical chlorite which is currently not available on the German drug market, first in 2002 and then in 2003. The 4.5 g% (m/m) drug concentrate is donated to Afghan institutions by WM e. V.

For ACL ulcers with crusts, the GMS meanwhile uses a polyacrylate hydrogel with 0.045% pharmaceutical chlorite (DAC N-055), which the WM e. V. member and pharmacist, [name], Emeritus Professor of the Pharmaceutical Faculty in Freiburg, proposed in slight modification of a DAB formulation.

Pharmaceutical sodium chlorite hydrogel has been used meanwhile by the GMS in Kabul to promote healing of more than 80 chronic ACL ulcers with dry crusts.

As an alternative to the SbV treatment, the GMS started to treat fresh ACL nodules with **electrocauterisation (EC)** on a pilot basis since the beginning of 2003, as it was believed that such heat treatment could reduce the number of parasites allowing the immune system to cope with the remaining protozoa in a more efficient manner. Limiting dilution analyses carried out at the Department of Medical Microbiology and Hygiene, University Hospital of Freiburg, showed that the *Leishmania* parasites were still present in the tissue when the punch biopsy was taken under local anaesthesia shortly after EC before starting moist wound treatment (MWT).

Interestingly in 2004, the Dutch NGO in Kabul, HEALTH*Net* International, which cooperates with the London School of Hygiene & Tropical Medicine, filed a final report on a randomised controlled trial to test the efficacy of thermotherapy (TT) at 50 °C (TT without cauterisation) against *Leishmania tropica* versus intralesional and systemic SbV therapy. Based on Giemsa smears with PCR confirmation of Leishmania etiology in 10% of the enrolled patients, they found that TT (69.4 % cure rate after 3 months, mean duration to cure 43.46 days) was as effective as intralesional SbV (75.3 % cure rate after 3 months, mean duration to cure 58.9 days) and more effective than i. m. SbV (44.8% cure rate after 3 months, mean duration to cure 49.46 days). They enrolled 406 patients, but their total drop out rate during a follow-up period of 3 months was 36.2 % in Kabul.

When the GMS subsequently treated the EC wounds of their patients with 0.045% DAC N-055 containing hydrogel, this led to a complete epithelialization of the majority of lesions with depigmentation and edge flattening mostly within 4 weeks. Giemsa smears, which were found to be *Leishmania*-positive before EC, turned *Leishmania*-negativewithin 7 days and stayed negative until complete healing. The punch biopsies of two of such lesions were transported from Kabul to Freiburg within 48 hours in *Leishmania* growth medium, where they were subsequently found *Leishmania*-negative in limiting dilution analyses. However, in chronic ulcers which had not been pre-treated by EC, in some cases a discrepancy was found between Giemsa smears which had turned *Leishmania*-negative and limiting dilution analyses which remained *Leishmania*-positive.

**Methods**

**Study location**

The clinical study will be carried out at the GERMAN MEDICAL SERVICE (GMS), Darwaze-e Lahory (DL) clinic, in Kabul, Afghanistan. The clinic has been operating for more than two decades. Being mainly involved in leprosy and tuberculosis programs, the DL clinic also focuses on dermatological patients. 23.5% of all patients seen in 2003 presented with cutaneous leishmaniasis. Recently, the DL clinic has accumulated a lot of experience in moist wound care management with dressings and digital photo documentation of as many as 50 patients per day.

**Study design**

1. The study will be a **randomized controlled double-blind trial**. Neither of the two groups is a placebo group, which would be unethical considering the dermatological virulence of *L. tropica*, because EC and moist wound treatment (MWT) have been seen to exert a therapeutic effect (GMS, unpublished results) similar to thermotherapy (“A randomized controlled trial to test the efficacy of thermotherapy against *L. tropica*”. Final report 2004, Health*Net* International, Kabul).

Since early 2003, electrocauterisation (EC) has become a routine therapeutic alternative to SbV injections for ACL patients at the GMS DL clinic. If initial EC is combined with subsequent MWT, this leads to cosmetically more acceptable healing results in a shorter time. It promotes granulation and in the ongoing open prospective pilot trial MWT promises to be more effective (3 relapses out 87 cured cases) than subsequent dry wound care with disinfectants (3 relapses out of 24 cured cases).

To elucidate the drug factor in MWT, a randomized double blind trial comparing electrocauterisation (EC) followed by moist wound treatment with or without 0.045% DAC N-055 in sodium polyacrylate hydrogel is to be undertaken now in patients with ACL lesions.

1. **Study patients, inclusion and exclusion criteria**

Eligible are patients attending the GMS DL clinic, who present at least one suspected ACL lesion on their arms or legs with no other skin diseases or infections and who have never been previously treated by SbV injections or any other form of anti-leishmanial medication. The lesions must be in the non-ulcerated stage.

Other inclusion criteria are a minimum age of 18 years, male sex and a laboratory confirmation of ACL by Giemsa stained wound smears before treatment.

Female patients and children are excluded from the trial to limit drop-outs due to the fact that for sociocultural reasons the treatment of women in Afghanistan might be too complicated as they normally require a male escort and that the skin lesion biopsies might deter children and females from returning for the follow-up appointments. Further exclusion criteria are the presence of ACL lesion(s) on or immediately adjacent to the nose, lips or eyes and any kind of serious comorbidities.

1. **Sample Size**

In view of potential drop outs, 2 x 50 eligible patients are to be enrolled into this study within two weeks.

**Objectives**

The aim of the trial is to

- evaluate the clinical efficacy of two new topical treatment forms of ACL: electrocauterisation (EC) followed by moist wound treatment versus EC followed by moist wound treatment plus 0.045% pharmaceutical chlorite that has been used in three European countries (Germany, Austria and Switzerland) in wound care management for over 20 years
- judge whether early wound care management would present a viable improvement to the actual anti-parasitic treatments mostly neglecting the chronic wound problem and to evaluate its long-term effect on immunity through relapse control 6 months after wound healing.

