**Outcomes and efficacy endpoints**

Both forms of treatment, EC plus polyacrylate dressing with or without pharmaceutical chlorite DAC N-055, are expected to be beneficial for the patient. However the reactive oxygen intermediate carrier, pharmaceutical sodium chlorite, which has been proven to enhance tissue regeneration and to exert antimicrobial effects, could also have a beneficial effect against the *Leishmania* parasite invader. This is to be checked as follows:

The time of complete wound healing is registered for each wound. After a maximum of 60 days of MWT the number of all healed wounds (complete epithelialization documented by photo) is registered versus the number of all wounds still open at that time. The parasite load is determined by limiting dilution analysis (see below) in a 2nd skin biopsy taken after complete healing or on day 61 after EC, if the wound has not healed completely.

GMS plans a late control of the ACL patients after six months with photodocumentation, Giemsa smear and eventually a 3rd biopsy for LDA, if there is still a tissue infiltration but the Giemsa smear is Leishmania-negative and if the patient is willing to consent to this.

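### The objective of showing a long-term effect of early wound care on immunity cannot be met by one six-month relapse visit with no immune measurement and no arm without moist wound treatment

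*Combined protocol and SAP*

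**What the plan says.** The second aim in the Objectives section is to judge whether early wound care is a viable improvement and to "evaluate its long-term effect on immunity through relapse control 6 months after wound healing". In that sentence, *its* refers to early wound care.

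The measurement is described under Outcomes and efficacy endpoints: "GMS plans a late control of the ACL patients after six months", with photographs and a Giemsa smear. A third biopsy for limiting dilution analysis follows only if infiltration persists, the smear is negative and the patient agrees.

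The Background gives three relevant facts. Lesions appear "2 to 24 months after the transmission of" the parasite. Untreated lesions tend to "heal after one to two years without any treatment leading to a permanent immunity in ca. 90 % of the cases". In the other 10% "of the cases relapses with scant parasites in the lesion, an increased delayed type hypersensitivity (DTH) reaction" and/or antimonial resistance are described.

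Under Study design, the pilot result for moist wound treatment is "3 relapses out 87 cured cases", and both randomised arms receive electrocauterisation followed by moist wound treatment, with or without chlorite. Amendment 2 names time to complete healing as primary and 60-day parasite load as secondary endpoint. It gives relapse and immunity no endpoint, definition, test or sample size.

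**The concern.** The aim goes beyond what is measured. Photographs, smears and parasite cultures detect disease or parasites; none of them measures an immune response. The delayed-type hypersensitivity reaction is mentioned only as background. The aim concerns wound care, yet no randomised arm goes without it, so the design isolates only the added chlorite.

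At stake is what the report may conclude. A low relapse count at six months could be presented as evidence that early wound care preserves or induces immunity, and the data would not support that. The analysis of healing time does not depend on this aim.

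**Working it through.** **1. The plan's own sample size.** Amendment 2 assumes median healing of 28 and 14 days, 60 days of follow-up, 80% power and a 5% level (taken as two-sided).
- Exponential healing gives a hazard ratio of 28/14 = 2.
- Healed by day 60: 1 − 2^(−60/28) = 77.4% and 1 − 2^(−60/14) = 94.9%; mean 86.1%.
- Schoenfeld: 66 events, 66/0.861 = 76.6, or 39 per arm. Freedman: 71 events, 71/0.861 = 82.4, or 42 per arm.
- The stated 40 per arm is reproduced to within 2 patients, and 80/0.80 = 100. This calculation covers healing time only.

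**2. Aim against measurement.**

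| The aim needs | The plan provides |
|---|---|
| A measure of immunity | Photographs, Giemsa smear, conditional biopsy for parasite load |
| A comparator without early moist wound care | Moist wound treatment in both arms |
| A long horizon | One visit at six months |
| A definition and analysis | None for relapse or immunity |

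**3. Precision for relapse.** Assume 20% drop-out also holds at the late visit (50 × 0.80 = 40 per arm) and that patients healed by day 60 are the ones at risk.
- Healed and seen: 40 × 0.774 = 31 and 40 × 0.949 = 38.
- Expected relapses at 3/87 = 3.4%: 31 × 3/87 = 1.1 and 38 × 3/87 = 1.3.
- Exact (Clopper-Pearson) 95% intervals: 1/38 gives 0.1% to 13.8%; 1/31 gives 0.1% to 16.7%. Both include 10%.
- With no relapses, the upper limit is 1 − 0.025^(1/31) = 11.2% for 31 patients and 1 − 0.025^(1/38) = 9.3% for 38. Only the latter falls just below 10%.
- The Background cites 36.2% drop-out over three months in a Kabul trial. At that rate 50 × 0.638 = 31.9 per arm remain, of whom 31.9 × 0.774 = 25 and 31.9 × 0.949 = 30 have healed.

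**4. If immunity is taken to include protection against reinfection.** The documents give a range of 2 to 24 months but no distribution, so three shapes are assumed. F is the distribution function of the incubation time. An infection acquired s months after healing is visible at the check if its incubation is at most 6 − s. With infections spread evenly over six months, the visible share is (1/6) × the integral of F from 2 to 6.

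| Assumed shape | Visible if acquired on day of healing | Visible if acquired evenly over six months |
|---|---|---|
| Uniform | 4/22 = 18% | (4²/2)/22/6 = 6% |
| Triangular, mode at 2 months | 1 − (18/22)² = 33% | 11% |
| Log-uniform | ln 3/ln 12 = 44% | 17% |

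Extremes for the last column: every incubation exactly 2 months gives 4/6 = 67%; every incubation over 6 months gives 0%.

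With a constant infection rate, the complement is the share of new lesions in that window that stem from infection before healing: 83% to 94% under the three shapes, 33% to 100% at the extremes.

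**5. Mixing, only if new lesions were counted as relapse.** The documents give no infection rate. Assume a share q of 0.5% to 5% of patients develops a new lesion by the visit, and true relapse r = 3/87. Apparent relapse is 1 − (1 − r)(1 − q), which is 3.9% to 8.3%. The share that is not relapse is (apparent − r)/apparent, about 12% to 58%.

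**The case against.** The strongest reply is that the protocol uses immunity in a narrower sense. The Background sets "leading to a permanent immunity in ca. 90 % of the cases" against relapse in the other 10%, and places relapse in the lesion. On that reading, absence of relapse is a clinical proxy for host control of residual parasites. Incubation runs from transmission to first lesion and does not govern reactivation of a treated lesion, so the 2-to-24-month argument bears only on reinfection, which the objective does not mention. This stands, and step 4 is therefore conditional. It does not rescue the aim: a proxy at one visit, with about one event per arm and no arm without moist wound treatment, still cannot show a long-term effect of wound care.

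A reader might infer that new lesions elsewhere on the skin would be counted as relapse and so contaminate the result. The documents do not say so. Healing is documented by photograph, the late visit repeats photography, and Amendment 2 fixes a target lesion in patients with several and documents the rest. Site can therefore be traced; the rule is simply not written. Reinfection at the same site would remain unresolved. Between randomised arms, new-site lesions from earlier infection would mainly dilute a difference.

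A reader might also infer that the six-month visit has no value. That goes too far, since it can describe recurrence. Finally, because Amendment 2 gives relapse no test, the late visit is already descriptive in effect. That limits the consequence but leaves the stated aim in place.

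**Conclusion.** The objective as written cannot be delivered. The grounds that need no assumption are the absence of any immune measurement, the single visit, and moist wound treatment in both arms.

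The precision argument adds about one expected relapse per arm and an interval of 0.1% to 13.8% for 1/38. It rests on exponential healing, 20% drop-out carried to the late visit, and a pilot relapse rate whose follow-up length is not stated. The incubation argument applies only if immunity includes protection against reinfection, and it depends on the assumed shape: 6% to 17% visible, 0% to 67% at the extremes. Confusing new-site lesions with relapse is possible, not established.

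Severity is minor to moderate. The point changes what the trial may conclude about immunity and leaves the primary endpoint intact.

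**What to change.** - In the Objectives, replace the phrase on long-term immunity with: *recurrence at the treated lesion within six months of healing*.
- At the late visit, classify each lesion by site against the healing photograph. Activity at the treated site counts as recurrence; lesions elsewhere are tabulated separately as new-site lesions.
- Report recurrence per arm with exact 95% confidence intervals, labelled descriptive, with the number healed and seen at six months as denominator.
- Draw no conclusion on immunity or on wound care as such. Any between-arm statement concerns the added chlorite only.

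The cost is a change of objective wording and one line on the six-month form, with no extra visits, patients or assays, since the photographs are already planned. The downside is giving up the immunity claim.

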**Interventions**

1. **Skin biopsies**

Two punch biopsies are taken from every patient under local anaesthesia, the first before EC, the second after complete wound healing. One half of the 2.0 mm diameter cylinder is transferred into tubes with *Leishmania* culture medium under sterile conditions for limiting dilution analysis (LDA) within 48 hours to the Department of Medical Microbiology and Hygiene of the University Hospital of Freiburg. The second half is fixed in formalin for histopathology in Freiburg. For their second punch biopsy the patients will be examined in clusters. The second punch biopsy should be done within one week after complete healing to avoid drop outs. From wounds which have not completely healed after 8 weeks of MWT, a second biopsy will also be taken the following day.

1. **Electrocauterisation (EC)**

After intensive skin cleaning with water / soap first followed by rinsing with 70% ethanol and disinfection of the intact skin in both groups **A** and **B** with a 5% dilution of 4.5% (w/w) pharmaceutical chlorite plus 1.5 vol% acetic acid for 20 minutes, the nodule is locally anesthetized with 1% lidocaine. The whole nodule area is then electrocautered with a high-frequency electrosurgical Mini Cutter (HMC 80 HF Chirurgie) produced by Hüttinger Medizintechnik (D-79224 Umkirch) first using monopolar superficial coagulation and then monopolar deep coagulation for thermo-therapy starting with intensities from 4 to 6 depending on the thickness of the epidermis and using a broad blade and intensities between 5 and 7 after the skin has been opened.

**C. Moist wound treatment and wound dressings**

0.5 ml of 4.5% (w/w) pharmaceutical chlorite solution per 50 g jelly (which equals a concentration of 5 mM NaClO2) pH 7 and drug free jelly pH 7 are freshly prepared in the GMS laboratory every day according to the attached “mucilago” formulation. The pots with the hydrogels are marked jelly A and B without any further indication for the personnel doing the wound dressing. The jellies are applied directly to the wounds with a sterile syringe, which are then covered with gauze and closed with a layer of food preservative folia fixed with a bandage, after the whole skin area covered by folia has been intensively cleaned with 70% ethanol. Dressings are renewed every day with a weekly pause on Fridays. The wounds are checked for possible superinfections by Giemsa-stained wound smears. If dry gauze dressing for one day does not change the situation, systemic antibacterial treatment is given. Anti-leishmanial and topical co-medication is not allowed. If a patient is over-due for his daily dressings for more than two days, he/she is excluded from the trial.

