**Amendments to the original study protocol from June 12, 2004**

Amendment 1 (requested by the Ethics Committee of the University of Freiburg on July 28, 2004; submitted August 11, 2004; approved August 24, 2004): Informed consent of the patients

The patients will be informed orally by the doctors or the medical student about the planned diagnostic and therapeutic procedures. Specifically, they will hear about the advantages (e.g. more rapid cure, less infections, healing of the skin plus killing of the parasites) as well as the possible side effects of the new treatment (e.g. allergic reaction to the foil or the pharmaceutical chlorite) as compared to the established standard methods.

Amendment 2 (requested by the Ethics Committee of the University of Freiburg on July 28, 2004; submitted August 11, 2004; approved August 24, 2004):

Sample size and power calculation, randomization, primary and secondary endpoints

For this study, 100 patients shall be recruited, 50 in each treatment arm, eventually for technical feasibility reasons in a sequential order, 2 x 25 patients during the first 2 months and 2 x 25 patients during the following 2 months.

*Randomization* will be performed in two strata: patients with a single lesion and those with multiple lesions. In the latter case, one target lesion will be determined in advance for the primary evaluation; other lesions will be documented for further investigations.

*Primary endpoint* is the time until complete wound healing. Under the assumption that the median healing time is 4 weeks in the control arm and 2 weeks in the investigational arm and that the follow-up time is 60 days, a number of 40 patients each is necessary to obtain a power of 80% (significance level 5%). A presumed drop-out rate of 20% leads to the total number of 100 patients. Comparison of the study arms will be performed in the ITT population by means of the Log-rank test. Depending on the data, a more detailed analysis in a Cox Model including single/multiple lesions and parasite load at baseline as additional effects might be performed.

As a *secondary endpoint*, parasite load after 60 days will be compared in the PP population between the two study arms either by means of the Mann-Whitney-Wilcoxon test or in case that the distribution shows a singularity at zero, by means of the fourfold table chi-square test (dichotomized neg/pos).

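### Patients overdue for dressings are excluded from the trial, which conflicts with the intention-to-treat log-rank test named as primary and gives away observable healing times

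*Combined protocol and SAP*

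**What the plan says.** Under Interventions, the section on moist wound treatment and wound dressings sets the schedule, "Dressings are renewed every day with a weekly pause on Fridays", and then the rule: "If a patient is over-due for his daily dressings for more than two days, he/she is excluded from the trial". The Outcomes section allows up to 60 days of this treatment, so the rule can be triggered throughout that period.

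Amendment 2 sets the primary analysis. The primary endpoint "is the time until complete wound healing", and "Comparison of the study arms will be performed in the ITT population by means of the Log-rank test". The per-protocol population is named only for the secondary endpoint, parasite load. The amendment neither withdraws nor reinterprets the dressing rule.

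No section defines the intention-to-treat or per-protocol population, says whether an excluded patient is still observed for healing, or gives a censoring rule. The Statistical analysis section refers only to standard methods.

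**The concern.** An intention-to-treat comparison rests on keeping every randomised patient in his arm and observing his outcome as far as possible. The dressing rule does the opposite: it removes a patient because of what he does after randomisation. If exclusion from the trial means what it says, his healing time is not recorded even where he could still be seen.

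Two things are at stake. The first is precision, because healing events are lost. The second is possible bias, because attendance may be linked to the wound. The documents offer two routes by which exclusion could differ by arm:

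- Amendment 1 lists allergic reaction to the chlorite as a possible side effect, and only one gel contains chlorite (although both arms have a chlorite skin disinfection before electrocauterisation).
- Under the planning medians, control patients stay in dressings about twice as long and are exposed to the rule for longer.

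The protocol also expects attendance to be difficult. Of an earlier trial it reports that "their total drop out rate during a follow-up period of 3 months was 36.2 % in Kabul".

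**Working it through.** **1. Reproduce the plan's sample size.** Inputs from Amendment 2: "Under the assumption that the median healing time is 4 weeks in the control arm and 2 weeks in the investigational arm", "that the follow-up time is 60 days", 80% power, 5% significance, equal allocation. Assumptions: exponential healing (rate ratio 28/14 = 2) and a two-sided test.

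- Healed by day 60: control 1 − 2^(−60/28) = 0.774; investigational 1 − 2^(−60/14) = 0.949; mean 0.861.
- Events, Schoenfeld: 4 × (1.960 + 0.842)² / (ln 2)² = 65.3, so 66; 66/0.861 = 76.6 patients, 39 per arm.
- Events, Freedman: (1.960 + 0.842)² × (3/1)² = 70.6, so 71; 71/0.861 = 82.4 patients, 42 per arm.
- The plan states 40 per arm. Drop-out: 80/0.80 = 100.

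The figure reproduces. The inflation treats drop-outs as contributing nothing.

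**2. Power if losses were unrelated to arm and healing.** Schoenfeld: Φ(√D × ln 2/2 − 1.96). Freedman: Φ(√D/3 − 1.96). D is the number of events.

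| Patients analysed | Events | Schoenfeld | Freedman |
|---|---|---|---|
| 100 | 86 | 90% | 87% |
| 80 (20% deleted) | 69 | 82% | 79% |

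**3. Power when exclusion builds up over time.** Assume the same constant daily exclusion hazard h = 0.009 in both arms, unrelated to the wound, acting until healing or day 60. With healing rate λ:

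P(excluded) = h/(h + λ) × [1 − e^(−60(h + λ))]

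- Control, λ = ln 2/28 = 0.0248: 0.267 × 0.868 = 23%.
- Investigational, λ = ln 2/14 = 0.0495: 0.154 × 0.970 = 15%.
- Overall about 19%. An identical rule therefore removes more control patients, because they are exposed longer.
- Events observed: replacing h by λ in the numerator gives 0.637 and 0.821; 50 × 0.637 + 50 × 0.821 = 73.

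Simulated log-rank power, 50 per arm:

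| Handling of excluded patients | Power |
|---|---|
| Followed to day 60 | about 90% |
| Censored at exclusion | about 85% |
| Deleted | about 76% |

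Censoring agrees with the formula for 73 events: Φ(√73 × 0.693/2 − 1.96) = Φ(1.00) = 84%. Deletion does worse on the same events because it removes slow healers preferentially, and more of them from the control arm.

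**4. False-positive rate with no true effect.** Simulation, 50 per arm, median 28 days in both, two-sided 5% test. Full follow-up gives 5.0%. The slower half of an arm and an exclusion time uniform before healing or day 60 are assumptions.

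| Exclusion pattern | Deleted | Censored |
|---|---|---|
| 20% of one arm from its slower half, none in the other | about 15% | about 4% |
| 20% in each arm, slower half in one, random in the other | about 13% | 6 to 7% |
| Same pattern, 36% in each arm | about 51% | 13 to 17% |
| Exactly the slowest 20% of one arm, none in the other | about 58% | about 20% |

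Equal patterns at 20% in both arms gave no inflation with deletion (4.0% to 5.4%).

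**The case against.** A reader might infer that the intention-to-treat log-rank test cannot be carried out. The documents do not support that: all 100 patients can enter the test, with excluded patients censored at exclusion. A milder reading is also open. Amendment 2 postdates the dressing rule and names both populations, so the rule could be meant as a per-protocol or treatment-stop criterion. Nothing in the text says so, however, and its wording points the other way.

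A reader might also infer that the patients lost are a non-random group. That too is not shown. No section says how many would miss dressings, why, or whether this differs by arm. The rule is the same in both arms, the trial is described as double-blind, and the staff see only jelly A and jelly B. Informative loss is a plausible risk, no more.

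The sizes depend on assumed patterns and run from no inflation to severe inflation. The 36.2% is total drop-out over three months in a trial of other treatments, so it does not forecast exclusions here, and this protocol restricts enrolment partly to limit drop-out. The plan already allows for 20% loss, and power stays near 80% if that loss is unrelated to arm and outcome. Nor would full follow-up be free, or complete for patients who do not return.

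These points limit what can be claimed. They do not remove the conflict between a rule that excludes patients after randomisation and a primary analysis by intention to treat.

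**Conclusion.** The point holds as a conflict between the dressing rule and Amendment 2. Followed as written, the plan gives up healing times that could have been observed, and it does not settle whether excluded patients are deleted or censored. With about 19% excluded through a hazard unrelated to the wound, that choice moves power from about 90% (full follow-up) to 85% or 76%. Under deletion the 80% target is missed although the loss is within the 20% allowance. The allowance covers lost numbers; it does not protect against selective loss.

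Bias in the false-positive rate is conditional. With 20% exclusion drawn from the slower half of one arm, deletion gives about 15%, and censoring stays at or below about 7%. Heavier or more extreme selection makes both worse. All these figures rest on exponential healing and assumed exclusion patterns and are illustrations, not predictions. The matter should be settled before enrolment because healing times that were not collected cannot be recovered later.

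**What to change.** Reconcile the two sections and define both analysis populations. Suggested wording:

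*Being overdue for dressings by more than two days is recorded as a protocol deviation and removes the patient from the per-protocol set only. He stays in the trial and is followed for healing to day 60 with photo documentation, at the weekly smear visits where possible. He is analysed in his randomised arm in the intention-to-treat log-rank test. Follow-up is censored only at true loss to contact or at day 60. The number of overdue patients and the reasons are reported by arm.*

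Whether dressings continue for such a patient is left to the clinicians; the wording governs follow-up and analysis only.

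Costs: a short protocol change and some effort to recall patients. Healing will be dated more coarsely for overdue patients seen weekly than for those seen at daily dressings. The estimate may look slightly less favourable because it includes less adherent patients. Patients who cannot be reached will still be censored, so the 90% is an upper limit.
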